### Recruitment

Identification and recruitment will be by a healthcare professional on admission to one of four inpatient Stroke Rehabilitation Unit participating in the trial. This will be supported by the local NIHR Clinical Research Network. The healthcare professionals will log all admissions and screen patients for their stroke severity. All patients classified as a severe stroke will be screened for their eligibility, and any eligible participants will be approached within 48 h of the participant being deemed medically fit for rehabilitation or as soon as practicable.

## Methods: assignment of interventions

### Randomisation and concealment

The randomisation process will follow a strict and auditable protocol. Randomisation will take place after all baseline assessments have been carried out; the blinded assessor will input relevant participant details into the trial website, and randomisation will subsequently be conducted by the Peninsula Clinical Trials Unit (PenCTU) data programmer via the secure web-based system. The allocations will be computer-generated by the PenCTU in conjunction with an independent statistician, in accordance with the PenCTU’s standard operating procedure. The randomisation list and the program that generated it will be stored in a secure network location within the PenCTU, accessible only to those responsible for provision of the randomisation system. This will ensure concealment of both the clinical staff undertaking recruitment and the blinded assessor to each participant’s allocated group.

A minimisation procedure (which has a random element) during the randomisation process will be used to reduce possible imbalance between the two groups (intervention and control). Minimisation factors are:Fatigue scored by the participant (if they are able) at baseline assessment, as measured using a Visual Analogue Scale (VAS) (fatigue (VAS: 4–10) vs. no/minimal fatigue (VAS: 0–3)) (Additional file 3)Presence of OH at baseline, tested using manual sphygmomanometer and a standardised protocol

After randomisation, an automatic email will be sent by PenCTU to the relevant treating physiotherapist to notify them of each participant’s allocated group. Notification that randomisation has taken place (but no details regarding individual participant’s allocated group) will also be sent to the CI. Access to the randomisation code and allocation list will be confined to the CTU data programmer; no one else in the trial team will be aware of participant’s allocated group until formal randomisation is completed, hence maintaining effective concealment.

### Blinding

Trial participants and treating physiotherapists are unable to be blinded due to the nature and complexity of the intervention. However, the assessors undertaking the outcome assessments will be blinded to all participant’s allocated group until after the 3-week assessments have been completed. To undertake the qualitative evaluation, one assessor will be unblinded to group allocation for up to 16 participants. A member of the research team who does not require to be blinded will undertake the stratified purposive maximum-variation sampling.

The initial baseline assessment will be undertaken once consent/assent has been received and prior to randomisation. Every effort will be made throughout the trial to ensure assessments are blinded for the remaining 34 participants whose allocated group will not be unblinded. Treating physiotherapists and/or participants will be reminded not to discuss their allocated group with the assessor during any interaction. At each assessment time point, the blinded assessors will be asked to record if they were unblinded to group allocation, and if so, the reasons for this as well as recording which group they think the participant was allocated to.

## Methods: data collection, management, and analysis

Data will be collected using a range of methods: semi-structured interviews with patient participants, their relatives, and treating physiotherapists/PIs, Case Report Forms and observer completed fidelity checklists.A)Feasibility outcomes

**Table Taba:** 

Feasibility indicator	Outcome measures	Data collection method
Process		
Recruitment rate	% of participants recruited/time	Case Report Forms
Retention rate	% of participants completed T1, T2, T3, T4, T5	Case Report Forms & Withdrawal Forms
Ability to consent	% of participants consenting	Screening/Approach Logs
Consent rate	% of consultee declarations	Case Report Forms
Eligibility criteria	% of admissions screened & eligible	Screening/Approach Log, Recruitment rate, Interview & Focus Group
Willingness of physiotherapists to recruit	% of admissions screened & approached	Recruitment rate, Interview & Focus Group
Willingness of patients to be randomised	% of participants who refuse to enrol in the trial	Recruitment Rate, Interviews & Focus Group
Acceptability of the intervention	% of withdrawals	Case Report Forms & Interview
Determining usual physiotherapy	Frequency specific physiotherapy interventions are implemented	Case Report Forms
Resources		
Burden	% of participants refusing physiotherapy sessions and follow-up assessments	Case Report Forms & Interviews & focus group
Cost effectiveness	*n* = duration (minutes) of functional standing frame programme session	Case Report Forms & Interviews
Management		
Fidelity	Observe intervention and control group sessions	Fidelity Checklists
Participant adherence	*n* = sessions per week	Case Report Forms
	*n* = minutes in standing	Case Report Forms & interview
	*n* = sit to stand repetitions	Case Report Forms & interview
	*n* = Yes; *n* = No for enjoyment	Case Report Forms & interview
	Score out of 10 for effort	Case Report Forms & interview
	Score out of 10 for fatigue	Case Report Forms & interview
Orthostatic hypotension protocol	% incidence of orthostatic hypotension	Case Report Forms
	% of incomplete sessions due to orthostatic hypotension (OH)	Case Report Forms
Safety		
Intervention	*n* = AE & SAE	Adverse Event and Serious
Data collection	*n* = AE & SAE	Adverse Event Forms

T1: baseline; T2: post-intervention period; T3: 3 months; T4: 6 months; T5: 12 monthsB)Clinical outcome measures

Standardised, validated clinician-rated and patient self-reported clinical outcomes will be measured in both groups at baseline, post-intervention (within 1 week) and follow-up (3, 6 and 12 months ± 1 week). Assessments at these time points will be conducted wherever the participant is residing. Due to the average length of stay in inpatient stroke rehabilitation, follow-up assessments at 3, 6 and 12 months are likely to be in the participants’ own home or residential/nursing care facility. All the outcome measures listed below will be undertaken at each of the follow-up trial visits.

### Economic evaluation

As this is a feasibility trial, an economic evaluation will not be carried out. However, the data set for the EQ-5D 5L will be collected to determine if it is feasible to collect these data from people with severe stroke.

### Process evaluation

Process evaluation is a key part of the intervention development process to enable conclusions to be made about the strengths and weaknesses of a trial. This will facilitate decision-making for the definitive main trial. The Medical Research Council guidance [43] recommends process evaluation and highlights the importance of capturing fidelity (whether the intervention was delivered as intended); dose (the quantity of intervention implemented) and reach (whether the intended target population comes into contact with the intervention, and how).

Fidelity will be measured using several mechanisms: (i) treating physiotherapists will record the content of their physiotherapy sessions and adverse events in the Case Report Forms; (ii) an independent assessor will observe one intervention and one control group session at each of the four Stroke Rehabilitation Units at random timepoints during recruitment and complete a fidelity checklist (Additional file 4); (iii) during qualitative interviews with treating physiotherapists.

### Data analysis

A detailed statistical analysis plan will be developed by the lead author and approved by statisticians and the Trial Steering Committee, prior to the final database lock and analyses. The primary descriptive analyses will be on an intention to treat basis. The analyses of the quantitative data will be in two stages, in line with CONSORT guidelines for pilot and feasibility trials [21].*Stage 1* will summarise the feasibility outcome data.*Stage 2* will summarise the clinical outcome data at each time point. Descriptive statistics of the clinical outcome data will be produced for each trial arm. No formal hypothesis testing will be undertaken of the data.

### Qualitative analysis

The qualitative data will be transcribed verbatim and analysed using thematic analysis [9], using a framework matrix as a data management tool [58, 59].

The qualitative data will be transcripts from one-to-one semi-structured interviews with patients, their relatives and physiotherapists, and the physiotherapist focus group. Anonymised transcribed data will be entered into NVivo software [50]. Narratives generated from the interviews will provide information about the uncertainties and unknowns of this feasibility trial. Interview and focus group participants (patients, relatives and physiotherapists) will be invited to review an initial draft to ensure the analysis represents an accurate overview of participants’ views, experiences and recommendations.

### Safety monitoring

Throughout the trial, all possible precautions will be taken to ensure participant safety and wellbeing. Patient participants will be monitored for adverse events via completion of an aphasia friendly brief interview after every therapy session during the 3-week intervention period. Treating physiotherapists will be asked to report adverse events related to the interventions (e.g. falls, musculoskeletal aches and pains, fatigue) and all serious adverse events (e.g. prolonged/required hospitalisation, life threatening event, death, significant medical event, persistent/significant disability/incapacity) to the research team, regardless as to whether they are thought to be related to the intervention or not and whether they believe these serious adverse events are related to the intervention or not. Additionally, participants will be monitored during their scheduled follow-up visits for adverse events and serious adverse events. Adverse events will be reviewed regularly by the Trial Management Group to determine the relatedness of these events to the intervention. Serious adverse events will be reviewed by the Trial Steering Committee.

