### Safety

#### Intervention

Safety of the intervention will be measured by the number of adverse events and serious adverse events that occur during the SPIRES intervention period (e.g. falls, skin damage, infection, hospital admission, death). The treating physiotherapists are responsible for documenting any adverse events or serious adverse events.

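### The protocol article gives the unblinded treating physiotherapists two conflicting rules on which non-serious adverse events to report

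*Protocol article*

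**What the plan says.** Two places in the protocol article set the rule for the same staff and the same period.

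**Objectives, Safety, Intervention.** The outcome is defined without regard to cause: "Safety of the intervention will be measured by the number of adverse events and serious adverse events that occur during the SPIRES intervention period". The examples given there include skin damage and infection as well as falls. The duty that follows is also unrestricted: "The treating physiotherapists are responsible for documenting any adverse events or serious adverse events". The table of feasibility outcomes lists the measure as the number of adverse events and serious adverse events, again with no condition on cause.

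**Safety monitoring.** The reporting instruction begins: "Treating physiotherapists will be asked to report adverse events related to the interventions (e.g. falls, musculoskeletal aches and pains, fatigue". It continues: "and all serious adverse events (e.g. prolonged/required hospitalisation, life threatening event, death, significant medical event, persistent/significant disability/incapacity) to the research team". It then closes with a doubled clause: "regardless as to whether they are thought to be related to the intervention or not and whether they believe these serious adverse events are related". The section later says who decides on cause: "Adverse events will be reviewed regularly by the Trial Management Group to determine the relatedness of these events to the intervention".

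**Blinding.** On those doing the reporting: "Trial participants and treating physiotherapists are unable to be blinded due to the nature and complexity of the intervention". The section on the control arm adds that the same physiotherapists are expected, though not required, to deliver both arms.

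**The concern.** Safety is one of the four feasibility domains, and its outcome is a count. A count can be interpreted only if everyone who contributes to it applies the same entry rule. Here one section admits every adverse event, and another appears to admit non-serious events only after the physiotherapist has judged them related to the interventions.

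That judgement would be made by someone who knows the allocation, and before the Trial Management Group sees the event. It is also hard to apply evenly. Fatigue or a fall is readily linked to a new standing-frame programme. It is less readily linked to usual physiotherapy, for which the article itself says there is no agreed definition. Staff on four Stroke Rehabilitation Units could each settle the ambiguity in their own way.

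At stake are the completeness of the non-serious event count and whether it means the same thing in both arms and on every unit.

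**Working it through.** The document gives no figure on this point, so there is nothing to reproduce or recompute. The check is a comparison of the texts.

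**Step 1: the rules side by side.**

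| Element | Objectives (Safety, Intervention) | Safety monitoring |
|---|---|---|
| Non-serious events | any event documented, all counted | those related to the interventions |
| Serious events | any event documented, all counted | all |
| Who judges relatedness | not a condition of counting | Trial Management Group, after reporting |

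The serious-event rows agree and the non-serious rows do not. In the Safety monitoring sentence the word *all* stands before the serious events only. The natural reading is therefore that the non-serious events are restricted.

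**Step 2: can the closing clause remove the conflict?** It has two possible scopes.

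- *Serious events only.* The restriction on non-serious events stands, the sentence conflicts with the Objectives, and the first judgement of relatedness is made by an unblinded reporter.
- *Serious and non-serious events.* The rule then agrees with the Objectives. But the sentence asks for related events whether or not they are thought to be related, so its opening condition has no meaning. The second half of the clause, which names serious events specifically, makes this scope uncertain.

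Neither scope leaves a sentence that is both clear and consistent with the Objectives.

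**Step 3: test it on a case.** Take non-serious skin damage, or an infection, that a physiotherapist believes has nothing to do with therapy. Both kinds of event are among the examples in the Objectives, so the event counts and must be documented. Neither is among the non-serious examples under Safety monitoring, and on the first scope the physiotherapist is not asked to report it. Two careful physiotherapists could act differently, and each could point to the protocol.

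**Step 4: the consequence for relatedness.** On the first scope relatedness is judged twice: by the physiotherapist as a condition of reporting, and then by the Trial Management Group. The second judgement cannot restore an event that the first kept from the group by this route.

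**Step 5: size.** Distortion would depend on the true event rate in each arm and on the share of events judged related in each arm. The document gives none of these. If the share were equal in both arms, the count would be too low but the proportional loss would be even. If the shares differed, the counts would differ for that reason alone, in either direction.

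**The case against.** The best defence is that the physiotherapists already have an unfiltered duty. The Objectives tell them to document any event, and the Process evaluation section has them record adverse events in the Case Report Forms with no condition on cause. A brief adverse-event interview follows every therapy session, with no stated restriction to related events. Scheduled follow-up visits also ask about events, and the first falls within a week after the intervention. The closing clause can be read to cover non-serious events, and its first half is largely redundant otherwise. Finally, the article condenses a full protocol. The adverse event forms are not shown and may settle the matter.

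Much of this stands, and it limits the point. A reader might infer that physiotherapists report *only* related events. That word is not in the text, and the documentation duty in the Objectives contradicts it. A reader might also infer that the trial's comparison of event rates between arms is biased. The document does not support that either: Data analysis rules out formal hypothesis testing, and the likely progression criteria contain no adverse-event threshold. Nor does anything show that missed sessions, and so missed interviews, would differ between arms, since both have the same target of at least 5 days per week.

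The defence does not remove the contradiction. It shows that an unfiltered rule exists elsewhere, and that is exactly why the Safety monitoring sentence conflicts with it. One could reconcile the two by supposing that every event is documented and only related ones are passed on, but the article does not say so. Even then, the Trial Management Group would be judging relatedness among events already selected for it. The forms may clarify practice, but the published text would still give two rules.

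**Conclusion.** The point holds as an internal contradiction in the reporting rule for non-serious adverse events, aggravated by an ambiguous clause and by reporters who know the allocation. Serious events are not affected, because both sections ask for all of them.

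The possible harm is a non-serious event count that is incomplete and uneven between arms and units. This assumes that at least some physiotherapists follow Safety monitoring on its natural reading and that the other recording routes do not recover what they leave out. The document neither confirms nor excludes either assumption. Size and direction cannot be determined, and zero distortion between arms is possible. What is established is a conflict in wording that should be corrected; an actual allocation-dependent loss of events is not demonstrated.

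**What to change.** Reword the reporting sentence under Safety monitoring to match the Objectives. For example: treating physiotherapists report all adverse events and all serious adverse events in both arms during the intervention period, whatever the believed cause; the Trial Management Group assigns relatedness afterwards. Delete the doubled closing clause, which then has no function. Check that the adverse event form and the site training carry the same rule.

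The cost is one sentence, plus more non-serious event forms for 50 participants over 3 weeks. No treatment or clinical management rule changes.

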### Retention rates and withdrawal

Each participant has the right to withdraw voluntarily from the trial at any time, without any effect on their current or future care. This may be through personal choice (i.e. they withdraw their consent), where it becomes impossible to provide outcome data or comply with any other trial procedures for whatever reason, following consultation/recommendation of a health professional following an adverse event or serious adverse event, or a significant protocol deviation, such as a participant being found to be ineligible post-randomisation. Participants found to be ineligible will be withdrawn. Reasons for withdrawals will be recorded and reported by the treating physiotherapist using a standardised proforma. Participants who wish to stop participating in the functional standing frame group will be asked to remain in the trial for follow-up assessments as per protocol if this is possible, although it is acknowledged that if a participant is receiving end of life care this would not be appropriate.

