### Control (usual physiotherapy)

This is defined as routine physiotherapy stroke rehabilitation for 45 min per day (or as long as tolerated) for a target of a minimum of 5 days per week, which is aligned with RCP Guidelines [34]. There is no agreed upon definition of what constitutes usual physiotherapy; thus, there is likely to be variation in usual physiotherapy due to physiotherapists’ preferences, experience and training. Physiotherapists will record activities undertaken during every session using the Physiotherapy Content Recording Tool (Additional file 2) to enable description of usual physiotherapy across all four Stroke Rehabilitation Units. It will also capture any instances of protocol deviation where physiotherapists implement a standing frame programme with participants in the control group. The protocol, and face-to-face training sessions, advise physiotherapists not to change their usual physiotherapy practice.

It is expected, although not required, that the same physiotherapists will be delivering both interventions (e.g. implementing both the functional standing frame programme and usual physiotherapy). Clear instructions about content of the intervention and control group, combined with fidelity checking, aim to avoid any conflict. However, potential for bias is acknowledged, and therefore, a stepped wedge cluster RCT [28] may be considered for the future main trial. This would allow every site (cluster) to deliver both the control and the intervention, with every cluster switching from control to the intervention, but at different time points.

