### Sample size

As a feasibility trial, a formal sample size calculation based on considerations of power is not appropriate; this trial is not statistically powered to detect between-group clinically meaningful differences in a primary outcome. One of the objectives of this trial is to provide robust estimates of the likely rates of recruitment and follow-up, as well as provide estimates of the variability of the proposed primary and secondary outcomes to inform sample size calculations for the planned definitive trial. There is no consensus on the recommended number of participants required for a feasibility trial, with published “rules of thumb” ranging from 20 to 70 or more participants, when the planned primary outcome is of a continuous nature. A recent paper recommended a feasibility trial sample size should recruit 25 participants per allocated group, if the planned definitive trial will have a two-arm parallel group design, with 90% power and two-sided 5% significance level, to detect a “small” standardised effect size [71]. Therefore, this feasibility trial aims to recruit 50 participants in total.

A target sample size of 50 patient participants will allow the follow-up rate to be estimated to within ± 15%. The follow-up rate at 12 months is estimated to be 70%, which would provide follow-up outcome data on a minimum of 35 participants across both allocated groups and three sites.

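### Participants found ineligible after randomisation are withdrawn from the trial with no provision for follow-up, which conflicts with the intention-to-treat basis and feeds rule-driven losses into the retention and acceptability measures

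*Protocol article*

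**What the plan says.** All references are to the protocol article.

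- *Retention rates and withdrawal* lists ways in which a participant may leave the trial. One is "a significant protocol deviation, such as a participant being found to be ineligible post-randomisation". It then adds a flat rule: "Participants found to be ineligible will be withdrawn". The rule is the same for both arms.
- The same section says: "Participants who wish to stop participating in the functional standing frame group will be asked to remain in the trial for follow-up assessments", with an exception where end-of-life care makes this inappropriate. No matching request is stated for people found ineligible or for the control arm. Treating physiotherapists record and report the reasons for withdrawal.
- *Data analysis* says: "The primary descriptive analyses will be on an intention to treat basis". It also says: "No formal hypothesis testing will be undertaken of the data".
- *Retention rate* divides those completing each later assessment by those who completed T1, the baseline. *Randomisation and concealment* places baseline before randomisation.
- *Acceptability of the intervention* counts withdrawals asked for by the patient, a relative or a healthcare professional. The feasibility outcomes table gives the measure simply as the percentage of withdrawals.
- *Sample size*: "Therefore, this feasibility trial aims to recruit 50 participants in total"; "The follow-up rate at 12 months is estimated to be 70"%, giving at least 35 people with 12-month data, and the follow-up rate is to be estimated to within 15 points either way.

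**The concern.** Intention to treat has two parts: people are summarised in the arm to which they were randomised, and an effort is made to collect outcomes from all of them. The withdrawal rule leaves the first part possible but gives up the second for anyone found ineligible after randomisation. The section itself separates stopping a programme from leaving the trial, since people stopping the frame programme are asked to stay for assessments. Ineligible participants are placed on the other side of that line.

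No treatment effect is tested here, so the stake is the feasibility estimates. Retention, completeness of outcome measures and acceptability are what this trial exists to measure, and they will shape the definitive trial. An administrative removal says something about screening. It does not show whether patients tolerate the programme or will attend follow-up, yet under the stated definitions it lowers retention and may count against acceptability.

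There is also a possible imbalance. The 115 kg exclusion is tied to the standing frames, and blood pressure is checked before and during at least the first three frame sessions. The description of usual physiotherapy mentions no such checks. Ineligibility could therefore come to light more often in the intervention arm.

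**Working it through.** **1. Reproduce the plan's own figures.** Inputs from *Sample size*: n = 50, follow-up rate p = 0.70.

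- Expected 12-month completers: 0.70 × 50 = 35, as stated.
- 95% half-width: 1.96 × √(0.70 × 0.30 / 50) = 0.127, or 12.7 points. At p = 0.50 it is 13.9 points. Both are within the stated 15.

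**2. Follow an ineligible participant through the definitions.** Baseline is completed, so the person is in the retention denominator. Randomisation follows, ineligibility is found, and the person is withdrawn. They cannot then enter the numerator at any later assessment. In the acceptability measure they are a withdrawal under the table's wording. Under the text's wording they are one if the removal is treated as requested by a healthcare professional.

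**3. Size of the effect on retention.** The protocol gives no number of such cases, so w is assumed to lie between 1 and 5 of 50. Assume also that all are withdrawn before the 12-month visit and that the 70% rate applies to everyone else.

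Retention = 0.70 × (50 − w) / 50; fall = 0.70 × w / 50.

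| w (assumed) | 12-month completers | Retention | Fall from 70% |
|---|---|---|---|
| 1 | 0.70 × 49 = 34.3 | 68.6% | 1.4 points |
| 3 | 0.70 × 47 = 32.9 | 65.8% | 4.2 points |
| 5 | 0.70 × 45 = 31.5 | 63.0% | 7.0 points |

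If the 70% already allows for such removals, the total does not move, but part of the loss is still created by the rule.

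**4. Precision.** If five people were instead dropped from the denominator, the half-width at 70% would be 1.96 × √(0.21 / 45) = 13.4 points, still within 15. Precision is not the problem; what the rate measures is.

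**5. After the fix.** With everyone randomised kept in follow-up and in the summary, the plan's figures stand unchanged: 50 summarised, 35 expected at 12 months, half-width 12.7 points.

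**The case against.** The strongest reply is that withdrawal from the trial is not exclusion from analysis. Nothing says that data already collected are discarded or that anyone leaves their allocated group, and the handling of withdrawn participants is properly left to the analysis plan, which is promised but not shown. This stands in part: it is why the two sections are in conflict rather than in flat contradiction. It does not answer the main point, because an analysis plan cannot supply outcomes that were never collected.

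A second reply is that controls receive routine physiotherapy, so the frame programme is the only trial-specific treatment to stop, and outcomes are to be measured in both groups at every time point. That is a fair reading of why one arm is named. The wording still leaves a control participant who stops therapy without a stated request to stay.

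A third is that reasons for withdrawal are recorded, so counts by reason can be produced. This also stands, and it makes the reporting change cheap.

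A reader might infer more than the text supports:

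- *That any significant deviation leads to withdrawal, so that contaminated controls are removed.* Only ineligibility carries the mandatory rule; a significant deviation is a possible route. On frame use in controls the protocol says only: "It will also capture any instances of protocol deviation where physiotherapists implement a standing frame programme with participants in the control group". It does not class this as significant or link it to withdrawal.
- *That people are removed unevenly by arm.* The rule is worded identically for both arms and no split is given. Uneven loss is a risk, not a stated fact.
- *That unblinded physiotherapists decide who is removed.* They are said to record and report reasons.
- *That the effect is 12 to 20 points, larger than the gap between the 70% planning value and the likely 80% completion criterion.* Those figures are 3/25 and 5/25, which puts every assumed removal in one arm. The 70% and 80% are whole-trial figures. Like for like, 3 to 5 removals give a fall of 4.2 to 7.0 points, below that 10-point gap.

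**Conclusion.** The point holds in this form: the mandatory withdrawal of participants found ineligible after randomisation, with no provision for follow-up, conflicts with the stated intention-to-treat basis and should be reconciled with it. It also builds rule-driven losses into retention and possibly into acceptability.

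The overall effect on 12-month retention is 1.4 points per such withdrawal, so 1.4 to 7.0 points for 1 to 5 cases. This rests on an assumed number of cases and on 70% follow-up among everyone else. A difference between arms is plausible but cannot be sized from the protocol. As the analysis is descriptive, the harm is to feasibility estimates and to the planning of the definitive trial, not to a test of efficacy.

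**What to change.** In *Retention rates and withdrawal*, separate stopping the allocated programme from leaving follow-up, and state that:

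1. participants found ineligible after randomisation are asked to remain in follow-up and are summarised in the arm to which they were randomised, unless they or their consultee withdraw consent for data collection;
2. the request to remain for assessments applies to both arms, keeping the end-of-life exception already stated;
3. three counts are reported separately for each arm: stopped the allocated programme, withdrew from follow-up, and found ineligible after randomisation. The last is kept apart when acceptability is judged.

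Whether treatment continues for someone found ineligible remains a clinical decision and is not addressed here.

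The cost is a wording change, one extra field on the withdrawal form and a few more follow-up visits for people already enrolled. Sample size and stated precision do not change.
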